### Post-treatment measures and schedule

The FAAM, NPRS, FABQ, PANAS, LExSES, and a side effect questionnaire will be administered at 1 week following enrolment. The demographic questionnaire, FAAM, NPRS, FABQ, PANAS, and LExSES will be administered at 4 weeks following enrolment, and mailed to subjects to complete at 6 months, 1 year, and 2 years following enrolment.

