### Data Analysis

The primary dependent variable for this study is FAAM score at 1 week, 4 weeks, 6 months, 1 year, and 2 years. Secondary dependent variables include NPRS, modified FABQ, PANAS, LExSES, and GROC scores at 1 week, 4 weeks, 6 months, 1 year, and 2 years. The independent variable is the manual therapy intervention condition. All other outcome measures will be assessed as potential covariates of treatment success, which is defined as the achievement of minimum clinically important change score on the FAAM for this study.

Descriptive statistics will be calculated for the data set, including frequencies, means, and standard deviations. Between and within-group comparisons will be made for outcome measurements at 4 weeks, 6 months, 1 year, and 2 years post-enrolment. Analysis of variance with appropriate post-hoc pairwise comparisons will be used to assess between-groups differences for continuous data. Statistical significance of between-group differences in categorical data will be assessed with chi square analysis. Pearson correlations and multivariate linear regression analyses will be performed to determine statistical significance of associations with treatment success and failure. An intention-to-treat analysis will be performed for subjects who drop out of the study after enrolment but prior to completion of all study procedures. Statistical significance of inferential statistical tests will be accepted at α≤.05.

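### The outcome definitions include 1 week but the between-group comparisons start at 4 weeks; for the side effect questionnaire that drops its only time point, and the one rule that literally reaches it makes it a covariate of treatment success

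*Protocol article*

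**What the plan says.** **Schedule** (Post-treatment measures and schedule). The 1-week battery ends with the only harm instrument that the article names: "and a side effect questionnaire will be administered at 1 week following enrolment". The later battery leaves it out: "The demographic questionnaire, FAAM, NPRS, FABQ, PANAS, and LExSES will be administered at 4 weeks following enrolment", and the same set is mailed at 6 months, 1 year and 2 years.

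**Outcome definitions** (Data Analysis). Both lists include 1 week: "The primary dependent variable for this study is FAAM score at 1 week, 4 weeks, 6 months, 1 year, and 2 years" and "Secondary dependent variables include NPRS, modified FABQ, PANAS, LExSES, and GROC scores at 1 week, 4 weeks, 6 months, 1 year, and 2 years". Side effects are in neither.

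**Rule for everything else** (Data Analysis). "All other outcome measures will be assessed as potential covariates of treatment success". Success is defined there as reaching the minimum clinically important change on the FAAM.

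**Times of comparison** (Data Analysis). "Between and within-group comparisons will be made for outcome measurements at 4 weeks, 6 months, 1 year, and 2 years post-enrolment". One week is not among them.

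**General methods** (Data Analysis). Descriptive summaries, frequencies among them, are promised for the data set. For categorical data: "Statistical significance of between-group differences in categorical data will be assessed with chi square analysis". Neither sentence names a variable or a time point.

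**The concern.** Two statements in the same section disagree about 1 week. The outcome definitions make it a time point for the primary variable and every listed secondary variable; the comparison sentence omits it. For measures repeated at 4 weeks and beyond, the cost is one time point. The side effect questionnaire is not repeated, so if the comparison sentence is followed, nothing about side effects is compared between groups.

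The covariate rule adds a second problem. Side effects are recorded after randomisation and may be caused by the assigned technique. Assessing them as a covariate of FAAM success treats a result of treatment as an explanation of response, and it does not estimate how often each technique causes them.

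The trial sets a thrust, a sustained traction and a hands-on control without that force against each other, and its Discussion says the control is there to separate manual contact and attention from applied force. Whether force, or its speed, brings more side effects is a question that the randomisation and the data already scheduled can address. A report that kept strictly to the stated rules could give FAAM results by arm and no side effect results by arm.

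**Working it through.** The article gives no harm rate, harm effect size or harm power, so there is no figure to reproduce. The point rests on reading the schedule against the analysis rules.

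**Step 1. Scheduled times against comparison times.**

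| Measure | Scheduled after baseline | In the comparison sentence | Lost |
|---|---|---|---|
| FAAM (primary) | 1 wk, 4 wk, 6 mo, 1 y, 2 y | 4 wk, 6 mo, 1 y, 2 y | 1 of 5 |
| NPRS, FABQ, PANAS, LExSES (secondary) | 1 wk, 4 wk, 6 mo, 1 y, 2 y | 4 wk, 6 mo, 1 y, 2 y | 1 of 5 |
| Side effect questionnaire | 1 wk | none | 1 of 1 |

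**Step 2. Role of the questionnaire.** It is not the primary variable and not a listed secondary variable. It appears under post-treatment measures, so the rule for all other outcome measures covers it if read literally. The only role that this rule gives is potential covariate of success.

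**Step 3. Does another sentence require a by-arm comparison?** The chi-square sentence and the descriptive sentence permit one. Neither requires it: the first names no variable, and the second speaks of the data set and not of the groups.

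**Step 4. What a by-arm table would deliver.** Group sizes are from the Subjects section: 63 recruited per group, and 52 as the size that the power statement needs. Side effect rates are assumptions. The 95% half-width for a risk difference is

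1.96 × √[p₁(1−p₁)/n + p₂(1−p₂)/n]

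| Assumed rates | p₁(1−p₁) + p₂(1−p₂) | n = 63 | n = 52 |
|---|---|---|---|
| 15% vs 5% | 0.1275 + 0.0475 = 0.175 | 1.96 × √(0.175/63) = 10.3 points | 11.4 points |
| 20% vs 10% | 0.16 + 0.09 = 0.25 | 1.96 × √(0.25/63) = 12.3 points | 13.6 points |
| 30% vs 10% | 0.21 + 0.09 = 0.30 | 1.96 × √(0.30/63) = 13.5 points | 14.9 points |

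If no one in an arm reports a given side effect, the one-sided 95% upper bound is 1 − 0.05^(1/n): 4.6% for n = 63 and 5.6% for n = 52.

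**Step 5. Could it be a confirmatory test?** Approximate power at two-sided 0.05 (the article does not state sidedness) is

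Φ{[|p₁−p₂| − 1.96 × √(2p̄(1−p̄)/n)] / √[p₁(1−p₁)/n + p₂(1−p₂)/n]}, where p̄ is the mean of the two rates.

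With n = 63 this gives 35% for 20% vs 10%, 46% for 15% vs 5%, and 81% for 30% vs 10%. Only a large difference would be detected reliably, so the table should be labelled descriptive.

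**The case against.** The strongest reply is that the comparison sentence cannot be an exclusion rule. Read as one, it would also bar comparison of the primary FAAM outcome at 1 week, which the same section defines as part of the primary variable. The missing week is then a general inconsistency and not a decision about harms. **This stands**, and it is why a reader who infers that harms are never to be compared goes further than the text. No sentence says so, and the chi-square and frequency sentences leave room for a by-arm table.

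Second, the covariate rule may be meant for range of motion, muscle testing and the balance test, which are measured and given no other analytic role. The secondary list is introduced as inclusive rather than exhaustive, and the lists are loose in any case: GROC is a secondary variable at every time point but is absent from the post-treatment schedule. **This stands in part.** The intent may well be narrower, but the wording covers all other outcome measures and nothing takes the questionnaire out.

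Third, safety tabulation is commonly left to a full protocol or SAP, and neither is shown. That would answer a complaint about silence. It does not answer this one, because the article states both a set of comparison times and a rule for unlisted measures, and an SAP written faithfully to them would carry both forward.

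Fourth, worsening could still appear by arm through pain scores, and through GROC if it is collected. True, but neither counts side effects.

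**Conclusion.** The point holds as an internal inconsistency with one badly fitting rule. The 1-week time point is in the outcome definitions and missing from the comparison sentence. This costs the repeatedly measured outcomes one of five time points and the side effect questionnaire its only one. The sole rule that literally reaches the questionnaire gives it a role unsuited to a harm measure. No stated rule requires a by-arm harm comparison, though one is permitted.

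Two stronger readings are not supported. The documents do not say that side effects will go uncompared, and they do not single out harms for exclusion. Collecting side effects at 1 week is not itself at issue: the manual technique is given only in the first two of the five sessions, both in the first treatment week.

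The size is moderate. No efficacy conclusion at 4 weeks or later is affected. What is at risk is a side effect comparison across all 189 planned subjects that would otherwise come from data already being collected. The precision figures rest on assumed rates and describe what a comparison would yield, not the size of an error.

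**What to change.** In Data Analysis:

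1. Add 1 week to the times of between-group comparison, so that they match the definitions of the primary and secondary variables.
2. Name the 1-week side effect questionnaire as a safety outcome and state that the covariate-of-success rule does not apply to it.
3. Report the number and percentage of subjects with side effects by randomised group, with risk differences and 95% confidence intervals, labelled descriptive. The choice of contrasts, the breakdown by type of side effect and any exact test can be left to the SAP.

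The cost is a few sentences and one table. No new data, visits or subjects are needed, and no treatment rule changes. The drawback is wide intervals, so an apparent absence of difference must not be reported as evidence of equal safety.

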## Methods/Design

### Subjects

Patients with post-acute ankle sprains will be recruited to participate in this study from multiple clinical centers across the United States. The Institutional Review Boards of the University of the Pacific (Stockton, CA, USA) and Des Moines University (Des Moines, IA, USA) approved this study protocol. This study protocol is registered with http://www.clinicaltrials.gov (NCT00888498).

Inclusion criteria for this study are age 16-60 years, onset of ankle sprain at least 2 weeks prior to enrollment, and Foot and Ankle Ability Measure Activities of Daily Living (FAAM ADL) subscale score less than or equal to 67 points (ie, respondent indicates ≥20% disability). Exclusion criteria involve current assisted ambulation (eg, cane or crutches); inability to bear weight through the affected extremity immediately after injury with tenderness to palpation of the medial and lateral malleolar zones, styloid process of the 5^th ^metatarsal, and navicular [36]; positive anterior drawer or inversion stress maneuver suggesting ligamentous laxity [37-39]; volume of the affected limb greater than 10% of the unaffected limb per water displacement volumetry [40]; previous history of ligament or bony reconstructive surgery to the ankle and foot; concomitant injury to other lower extremity joints; and inability to comply with the treatment protocol.

A total of 189 subjects will be recruited (n = 63 per group). A group size of 52 subjects will provide 80% statistical power to detect an 8-point (9.5%) difference in FAAM ADL subscale score based on Martin and colleagues' data[41], with additional subjects recruited to account for a 20% dropout rate [42]. This sample size ensures the study is powered to detect a statistically and clinically significant difference between groups using a 2-sample t-test (Figure 1).

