### Pre-Participation Screening Measures

#### Foot and Ankle Ability Measure (FAAM)

The FAAM is a self-report questionnaire consisting of a 21-item ADL subscale and 8-item Sports subscale, in addition to a global rating of self-perceived foot function from 0-100% [41]. This inventory demonstrates satisfactory internal consistency, validity, and score stability. Test-retest validity is satisfactory for use in research designs involving repeated measures (ICC_2,1 _= .87-.89). Minimum clinically important change scores have been identified for the ADL subscale (8 points) and Sports subscale (9 points) with respect to patient global rating of change.

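### The between-group ANOVA of FAAM scores names no baseline FAAM term, although every subject has one before randomisation; adjusting for it would gain precision at almost no cost

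*Protocol article*

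**What the plan says.** The Data Analysis section of the protocol article defines the outcome as a score, not a change: "The primary dependent variable for this study is FAAM score at 1 week, 4 weeks, 6 months, 1 year, and 2 years". On the explanatory side it says "The independent variable is the manual therapy intervention condition". The method for continuous data is "Analysis of variance with appropriate post-hoc pairwise comparisons will be used to assess between-groups differences for continuous data".

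Covariates are mentioned once, for a different purpose: "All other outcome measures will be assessed as potential covariates of treatment success". Success there means reaching the smallest FAAM change regarded as clinically important, so this sentence does not put baseline FAAM into the ANOVA of scores.

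The same section also states "Between and within-group comparisons will be made for outcome measurements at 4 weeks, 6 months, 1 year, and 2 years post-enrolment", which leaves room for some form of repeated-measures analysis.

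On incomplete follow-up it says "An intention-to-treat analysis will be performed for subjects who drop out of the study after enrolment". The Subjects section enlarges the groups for attrition, "with additional subjects recruited to account for a 20% dropout rate", and makes a FAAM ADL score of 67 or less a condition of entry.

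**The concern.** FAAM ADL is known for every subject before allocation and is the same instrument as the primary outcome. Leaving it out of the model puts between-subject differences that existed before treatment into the error term. Bias is not the issue, since randomisation protects the comparison. What is at stake is wider confidence intervals and lower power than the collected data could give, in a trial with little power to spare.

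A second, smaller matter is the intention-to-treat sentence. The principle is that everyone randomised is analysed in the group assigned. The sentence attaches it to subjects who drop out, and so leaves unsaid what happens to those who stay in follow-up but miss sessions or receive something else. The Treatment schedule section lets clinicians and subjects choose other treatment after the 4-week measurements, and three of the five primary time points come after that.

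**Working it through.** **Inputs from the protocol article.** Subjects section and Figure 1 legend: d = 0.4, alpha 0.05, 80% power, 2-sample t-test, 52 per group, target difference 8 FAAM ADL points. The SD is not stated; 8/0.4 = 20 is implied.

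**Assumptions.**
- Two-sided test, since sidedness is not stated.
- d = 0.4 is scaled to the SD of the raw follow-up score. The article does not say which SD was used.
- Baseline-to-follow-up correlation r between 0.3 and 0.7. The article gives none. Its FAAM section reports an ICC of .87-.89, but that is test-retest reliability ("Test-retest validity is satisfactory for use in research designs involving repeated measures") and is not used as r. The entry cut at 67 narrows the baseline range and may lower r.

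**Step 1: the plan's own figure.** At d = 0.4, two-sided 0.05 and 80% power, the normal approximation gives 99 per group (one-sided, 78). With 52 per group, the noncentral t distribution gives power of 52.4% two-sided and 64.8% one-sided. The stated 52 is therefore not reproduced. That is a separate defect; here 52.4% serves only as the starting point.

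**Step 2: effect of adjustment.** With baseline as a covariate the residual variance is multiplied by 1 - r², so the effective standardised difference is 0.4/√(1 - r²). The gain equals multiplying the sample size by 1/(1 - r²).

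| r | 1 - r² | Effective d | Equivalent sample multiple | Power, 52 per group | n per group for 80% |
|---|---|---|---|---|---|
| 0 | 1.00 | 0.400 | 1.00 | 52.4% | 99 |
| 0.3 | 0.91 | 0.419 | 1.10 | 56.3% | 90 |
| 0.5 | 0.75 | 0.462 | 1.33 | 64.5% | 74 |
| 0.6 | 0.64 | 0.500 | 1.56 | 71.4% | 63 |
| 0.7 | 0.51 | 0.560 | 1.96 | 80.8% | 51 |

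**Step 3: when adjustment would rescue n = 52.** The difference detectable with 80% power at 52 per group is d = 0.555. Setting 0.4/√(1 - r²) = 0.555 gives r = √(1 - (0.4/0.555)²) ≈ 0.69.

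**Step 4: does the gain depend on that mismatch?** No. If the true standardised difference were 0.555, so that 52 per group did give 80%, adjustment would still raise power to 83.6% (r = 0.3), 89.9% (r = 0.5) or 97.5% (r = 0.7).

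**Step 5: change scores and repeated-measures ANOVA.** If baseline enters only as a level of time, the between-group contrast is a difference in change. With equal SDs its variance factor is 2(1 - r), against 1 - r² for ANCOVA:

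| r | Change score, 2(1 - r) | ANCOVA, 1 - r² |
|---|---|---|
| 0.3 | 1.40 | 0.91 |
| 0.5 | 1.00 | 0.75 |
| 0.7 | 0.60 | 0.51 |

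The ratio 2(1 - r)/(1 - r²) = 2/(1 + r) exceeds 1 whenever r < 1, so ANCOVA is the more efficient. Below r = 0.5 the change score is worse than no adjustment at all.

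**The case against.** The strongest reply is that the article nowhere says the ANOVA is unadjusted. Within-group comparisons are planned, so a repeated-measures model is possible, and a condensed article may leave model terms to a fuller document. This stands in part: adjustment is not ruled out. But the outcome is defined as a score, treatment is the one independent variable named, and covariates appear only for treatment success. Nothing in the text puts baseline FAAM into the primary comparison, and Step 5 shows that a change-score or repeated-measures reading is still less efficient than ANCOVA.

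It is also fair that the size of the gain rests on an assumed r and on the meaning of d = 0.4. If d was scaled to an SD of change, the figures in Step 2 do not apply. An unadjusted ANOVA is valid in a randomised trial, so this is a question of efficiency, not of error.

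A reader might go further and infer that intention-to-treat is restricted to drop-outs, or that randomised subjects fall out of the primary comparison. The document supports neither. It contains no restricting word, and the sentence read literally keeps drop-outs in. Subjects would be lost only if the ANOVA used observed cases, which the article does not say; missing values could be imputed first. The handling of missing data and its sensitivity analyses are commonly left to the SAP, and the 20% attrition is already allowed for in the sample size.

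**Conclusion.** The point holds as an improvement in efficiency. The primary between-group comparison is specified without baseline FAAM, although that value exists for everyone. Under the assumptions above, adjustment cuts residual variance by 9% to 49% and raises power at 52 per group from 52% to between 56% and 81%. The direction is certain for any r other than zero, apart from the one degree of freedom spent. The size is not, because r is not in the document. Adjustment should not be presented as the cure for the mismatch between n = 52 and d = 0.4: that must be resolved on its own, and adjustment would close the gap only at r of about 0.69 or more.

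The intention-to-treat sentence is poorly framed and should be reworded, but it excludes no one.

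**What to change.** State that FAAM ADL is analysed with baseline FAAM ADL as a covariate. Either ANCOVA at each time point, or one longitudinal mixed model with arm, visit, arm-by-visit and baseline FAAM ADL, would do; the pairwise arm contrasts are then read from that model. Treat NPRS, modified FABQ, PANAS and LExSES in the same way, each with its own baseline. GROC is described under Baseline Measures but rates response to treatment, so it has no usable baseline.

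Replace the intention-to-treat sentence with: *All randomised subjects are analysed in the group assigned.*

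The cost is a change of wording and slightly more programming. No new data are needed, since the screening and baseline visits already collect these scores. The change should be fixed before outcome data are seen by arm.

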## Abstract

**Background:**

Ankle sprains are common within the general population and can result in prolonged disablement. Limited talocrural dorsiflexion range of motion (DF ROM) is a common consequence of ankle sprain. Limited talocrural DF ROM may contribute to persistent symptoms, disability, and an elevated risk for re-injury. As a result, many health care practitioners use hands-on passive procedures with the intention of improving talocrural joint DF ROM in individuals following ankle sprains. Dosage of passive hands-on procedures involves a continuum of treatment speeds. Recent evidence suggests both slow- and fast-speed treatments may be effective to address disablement following ankle sprains. However, these interventions have yet to be longitudinally compared against a placebo study condition.

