## Discussion

This study protocol describes a randomized, placebo-controlled clinical trial that measures the short-, intermediate-, and long-term effects of talocrural joint mobilization, manipulation, and placebo treatment for individuals with post-acute ankle sprains. Hands-on treatments that improve ankle DF ROM are hypothesized to cause related improvement in disability and mitigation of re-injury risks. We believe the study designed in this paper addresses methodological deficiencies in the manual therapy literature to date that interfere with our optimal understanding of best practices related to mobilization/manipulation in individuals with post-acute ankle sprains. Specifically, inclusion of a hands-on placebo control should allow for differentiation of generalized clinical benefit from manual stimulation and clinician attention versus iatrogenic force application. In addition, the length of follow-up measurements should allow for adequate estimation of the potential longitudinal effects of mobilization/manipulation during the post-acute injury period on re-injury rate. The methodological characteristics of this study should help generate high quality data that will further our collective understanding of best practices in manual therapy.

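### The ANOVA for FAAM, measured repeatedly to 2 years, names treatment as its only factor and no arm-by-visit contrast; one likelihood-based mixed model would serve better under either reading of the plan

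*Protocol article*

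**What the plan says.** All of this is in the protocol article.

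- Outcome (Data Analysis): "The primary dependent variable for this study is FAAM score at 1 week, 4 weeks, 6 months, 1 year, and 2 years".
- Factor (Data Analysis): "The independent variable is the manual therapy intervention condition". Time is not named as a factor.
- Visits compared (Data Analysis): "Between and within-group comparisons will be made for outcome measurements at 4 weeks, 6 months, 1 year, and 2 years post-enrolment". The 1-week visit is in the definition of the primary variable but not in this list.
- Method (Data Analysis): "Analysis of variance with appropriate post-hoc pairwise comparisons will be used to assess between-groups differences for continuous data". The type of ANOVA is not given.
- Significance level (Data Analysis): "Statistical significance of inferential statistical tests will be accepted at α≤.05".
- Aim: the abstract gives the gap in knowledge as "these interventions have yet to be longitudinally compared against a placebo study condition", and the Discussion describes a trial that "measures the short-, intermediate-, and long-term effects of talocrural joint mobilization, manipulation, and placebo treatment".
- Missing data: the Subjects section allows for 20% dropout, the 6-month, 1-year and 2-year questionnaires are mailed (Post-treatment measures and schedule), and the Data Analysis section commits to intention-to-treat for subjects who drop out.

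**The concern.** The article states the outcome, the factor, the visits and the test, and that set contains no contrast across time. Two readings are open, and each has a weakness.

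**Visit-by-visit ANOVA.** Each test shows whether the arms differ at that visit. None shows whether the difference at 2 years is smaller or larger than at 4 weeks. A result that is significant at 4 weeks and not at 1 year does not show that the effect faded, because the difference between the two effects has not been tested. Subjects who miss a late visit add nothing to that visit's analysis, although their earlier scores carry information about it.

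**Classical repeated-measures ANOVA.** This can include time, but it needs every visit for every subject. Someone who returns four of five questionnaires is lost altogether, which sits badly with an intention-to-treat commitment.

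At stake is any statement about how an effect develops over the 2 years, and some precision at the late visits.

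**Working it through.** **Inputs.** From the article: 52 evaluable subjects per group, an 8-point FAAM ADL difference, 80% power, α = .05 (taken as two-sided), 2-sample t-test. Assumed, because the article does not give them: equal between-visit correlation ρ of .3, .5 or .7, and a true effect that is the same at every visit.

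**The plan's own figure.** The Subjects section says "A group size of 52 subjects will provide 80% statistical power to detect an 8-point (9.5%) difference in FAAM ADL subscale score". With n = 52, 80% power needs d = 0.555, which is an SD of 8/0.555 = 14.4 points. No SD is stated, so this is solved back from the power claim. The legend of Figure 1 gives d = .4 instead (SD = 8/.4 = 20), and with n = 52 the power is then only about 53%. That mismatch is a separate matter. Both power levels are carried below.

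**Mixed significance when nothing changes.** Let p be the power at one visit and z = Φ⁻¹(p). With complete data, the arm differences at two visits have correlation ρ. Then:

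- P(both visits significant) = Φ₂(z, z; ρ)
- P(first significant, last not) = p − Φ₂(z, z; ρ)
- P(mixed over four visits) = 1 − P(all significant) − P(none significant)

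Example at p = .80, ρ = .5: Φ₂ = .687, so early-significant, late-not = .80 − .687 = .113. Over four visits, all = .556 and none = .033, so mixed = .411.

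| Power per visit | ρ | Mixed, four visits | First significant, last not |
|---|---|---|---|
| 80% | .3 | 49% | 13% |
| 80% | .5 | 41% | 11% |
| 80% | .7 | 32% | 9% |
| 53% | .3 | 72% | 20% |
| 53% | .5 | 60% | 17% |
| 53% | .7 | 46% | 13% |

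With the three-group omnibus F at d = 0.55, both active arms better by the same amount, simulation gives mixed patterns in 45%, 37% and 30%. An arm-by-visit test rejects wrongly in about 5% of trials in every constant-effect scenario.

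**What the arm-by-visit contrast can detect.** For the change between two visits, SD of change = 14.4 × √(2(1 − ρ)) and SE of the arm difference = SD of change × √(2/52). At ρ = .5 the SD of change is 14.4 and the SE is 2.82. A half fade, from 8 to 4 points, gives 4/2.82 = 1.42 and power of about 29%. At ρ = .3 the SE is 3.34 and the power about 22%; at ρ = .7 the SE is 2.19 and the power about 44%.

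**Gain from using incomplete subjects.** Assume five visits, with the proportion observed falling steadily from 100% at the first to 80% at the last. The variance of the 2-year arm mean from a likelihood-based model with unstructured covariance is lower than that of the mean of observed 2-year scores by about 3% (ρ = .3), 7% (ρ = .5) and 12% (ρ = .7). With complete data the per-visit contrasts would be the same, so the gain comes from the missing visits.

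**The case against.** The strongest reply is that the article does not say one-way, does not say that each visit is tested alone, and does not say that significance will be compared across visits. Between- and within-group comparisons are compatible with a group-by-time ANOVA. The stated hypotheses are of improvement in the short, intermediate and long term, and a contrast at each visit answers those directly. Where the article justifies the long follow-up, it points to re-injury, not to the course of FAAM. Finally, model form is often left to a full protocol or analysis plan.

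Most of this stands, and it limits the point. A reader might infer that the trial will judge durability by comparing p-values, and that this will mislead in a third to a half of trials. The documents do not support that. The misuse is not planned anywhere, and the 32-49% counts every mixed pattern over four visits, under an assumed effect and assumed correlations. The pattern that would actually be read as fading is much rarer.

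The reply does not remove the point. The article does more than leave a detail open: it names a single factor, a list of visits and a method, while presenting the trial as a longitudinal comparison. If repeated-measures ANOVA was meant, the loss of subjects with a missing visit takes the place of the first problem.

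**Conclusion.** The point holds in a limited form. As written, the analysis commits to no contrast over time and uses a method that, on either reading, suits repeated measurement with mailed follow-up poorly. Between-group effects at single visits remain estimable and answer the stated hypotheses; what lacks support is any claim that an effect fades or emerges.

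If such a claim were drawn from which visits are significant, a constant effect would give a mixed pattern in about 32-49% of trials and a false appearance of fading in about 9-13%. This rests on four visits, 80% power per visit and correlation .3-.7; at the d of .4 in Figure 1 the false-fading figure is about 13-20%. The precision lost at 2 years by visit-wise ANOVA is modest, about 3-12% of the variance under the assumed dropout. The matter should be settled before results are seen, but it does not undermine the trial.

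**What to change.** Replace the ANOVA for FAAM with one likelihood-based linear mixed model for the FAAM ADL score at 1 week, 4 weeks, 6 months, 1 year and 2 years, with arm, visit and arm-by-visit as fixed effects and an unstructured within-subject covariance. Subjects with some missing visits stay in, and the 1-week visit is brought into the comparisons. Report the arm contrasts at each visit with 95% CIs from this model. Allow a statement that an effect fades or emerges only from the arm-by-visit contrast with its CI, and say in advance that a non-significant interaction will not be read as proof that an effect persists.

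The cost is a change of wording and slightly more analysis work, with no new data. The downside is that durability claims become harder to make, because the interaction contrast has low power for a partial fade (about 22-44% for a loss of half the effect, under the assumptions above).
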